### Randomization and recruitment

Randomization will be done at the district level. There are thirteen districts and two town administrations. Among a total of districts and town administrations, six districts and/or town administrations in South Gondar Zone will be selected using the random.org software by considering the rule of thumb assumption that covers 40% of districts and town administrations. Thus, the selected districts/town administrations will be assigned to the intervention and control arms with a 1:1 allocation ratio. This means three districts or town administrations will be randomly assigned to the intervention arm, and the other three districts or town administrations will be assigned to the control arm. District or town size will not be considered in the randomization process. All health facilities in the intervention and control arms fulfilling the eligibility criteria will be included in the study. The eligibility criteria for the inclusion and/or exclusion of health facilities will be based on the availability of TB diagnostic and treatment services, including the microscope diagnostic service and DOT programs. Participants will recruit to the study when confirmed they have any form of TB and are registered to the DOT programs. Participants will enter into the trial individually based, and patients will recruit continuously until the desired sample size achieve. Recruitment of participants will be from July 1 to September 30, 2022. The statistician who allocated the intervention and control arms, an expert who assesses the outcomes, participants who will be assigned to intervention and control arms, and healthcare providers who provide TB care will not be aware of who were assigned to the intervention and control arms. The project manager and/or investigators will be unblinded.

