### Outcomes of interest

The study will have three outcomes of interest. The primary outcome is the TB case detection rate. The secondary outcomes of interests are diagnosis delay and costs of TB care. The case detection rate will be expressed as percentage. The diagnosis delay will be defined as the time interval between the onset of symptoms and the confirmation of TB diagnosis, which includes patient delay and health system delay. The cost of TB care will include both direct and indirect costs of the patient for TB care and treatment as collected from the patients themselves and their medical records. Direct costs include out-of-pocket payments for medical services (counseling, drugs, laboratory tests, X-rays, and hospital stays) and non-medical services such as transportation, food, and accommodation costs.

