#### Sample size calculation for TB detection rate

Since the case detection rate will be calculated by considering the WHO estimator for the year 2023 per 100,000 populations. Estimating the number of TB cases for that year will be computed by using total cases in the year/100,100 * total population found in the catchment area multiplied by 100, expressed as a percentage. Therefore, all cases that are confirmed as TB patients in the selected districts will be considered as the final sample size.

The number of clusters involved in the study was determined using the following formula [39]: The number of clusters (*K*) required in each arm for unequal cluster sizes was also determined using the formula [40]: *K* = *n* [1 + ((CoV2 + 1) *m* − 1) ICC]/*m*′], where Cov2 = coefficient of variation of 0.25, effective ICC value of 0.03 for cluster-level ICC value of TB detection rate, *n* = sample size under individual randomization, *m* = average number of individuals found in each cluster was 18. From 40 clusters, with unequal clusters for intervention and control arms, 24 clusters included in the intervention, and 16 clusters in the control arm.

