### Measurements

The case detection rate will be calculated as the number of cases notified divided by the number of cases estimated for that year, expressed as a percentage [41]. The WHO estimator for the year 2022 was 132 per 100,000. Estimating the number of TB cases for that year will be computed by using that year/100,100 * total population of the catchment area. Estimating the number of TB cases for that year will be computed by using total cases in the year/100,100 * total population found in the catchment area multiplied by 100, expressed as a percentage.

Patient costs and their annual incomes collected in Ethiopian birr will be converted to US dollars ($) with an average exchange rate for the dates during which data collection took place. The total costs will be considered the sum of the entire direct and indirect costs of TB illness to patients. Out-of-pocket payment for health care (medical) will be the direct payment made for medical care directly by individuals at the time of service using minus insurance reimbursement. Out-of-pocket costs will be a payment for formal medical services, informal traditional practitioners, clinics, health centers, pharmacies, and hospitals for medical services and products such as diagnosis, treatment, and medicine. Out-of-pocket payment net will be a total out-of-pocket payment (medical and non-medical) minus any reimbursement received for payments made. The direct costs will be calculated by the sum of any payment affected by medical and non-medical costs. The medical costs will be the sum of out-of-pocket payments for TB diagnosis and treatment made by TB patients in a given household buying medicines, payments for diagnostic tests, and net reimbursements. The direct non-medical costs were out-of-pocket payments for transport, accommodation, and food before and during TB diagnosis. An indirect cost is costs incurred as a result of TB healthcare seeking and hospitalization, during the TB episode. The total period of absence (in hours) will be multiplied by the hourly wage rate of the absent worker.

Catastrophic costs due to TB: total costs (indirect and direct combined) exceeding a given threshold of the household’s annual income, here defined as exceeding 20%, as recommended by WHO [42].

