### Data analysis

Descriptive statistics will be used to summarize the baseline data. A chi-square test will be performed to compare the baseline characteristics of the intervention and control groups. Comparisons of detection rate, diagnosis delay, and costs of TB care between and within the intervention and control groups will be done using independent samples and paired sample *t*-tests, respectively. The independent *t*-test will be also used for the knowledge and attitude of post-test results of practitioners.

Logistic regression analysis will be used to determine the factors associated with case detection rate and diagnosis delay. A univariable logistic regression model will be fitted, and variables having a *p*-value less than 0.25 in the univariable logistic regression model will be fitted into the multivariable models. Variables with a *p*-value < 0.05 in the multivariable logistic regression model can be considered statistically significant. Crude and adjusted odds ratio (OR) with 95% confidence interval (CI) will be calculated to measure the strength of association between the dependent and independent variables. The fitness of the logistic regression model will be checked using the Hosmer–Lemeshow goodness of fitness test at *p*-value > 0.05. Multicollinearity between explanatory variables will be checked by a variance inflation factor (VIF), and variables with a VIF > 5 will be excluded from the final models.

Generalized linear mixed models (GLMM) will be used to assess the impact of the intervention on the change of cost of TB care. This GLM enables us to accommodate the correlation of observations due to the pre and post-intervention measurements and clustering of individuals within randomly selected clusters. Model fitting will be checked before the analysis is done. The effects of potential confounding factors will be controlled. The variance of the cluster-level residual errors will be computed using the intercept-only model. The variation between and within the groups will be analyzed.

Subgroup analysis will be employed to explore whether there is evidence that the detection variation depends on certain patients or facility characteristics. Covariate adjusted analysis will also employ to refine the analysis of case detection variation in the intervention and control arms the fact that some baseline characteristics may be related to outcome and unbalanced between the groups.

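### The printed formula for the case detection rate contradicts its own definition, and the logistic regression planned for detection cannot be estimated from patients who are all detected cases

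*Protocol article*

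**What the plan says.** Outcomes of interest: "The primary outcome is the TB case detection rate". Measurements and Appendix 2 both define it in words as notified cases over the cases estimated for the year, as a percentage.

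Measurements then prints two formulas, both introduced as ways to estimate the number of TB cases. The first is the yearly rate over 100,100 times the catchment population. The second is "total cases in the year/100,100 * total population found in the catchment area multiplied by 100, expressed as a percentage", and it appears again in the sample size section for the detection rate. On the reference incidence, Measurements says "The WHO estimator for the year 2022 was 132 per 100,000", while the sample size section speaks of "considering the WHO estimator for the year 2023 per 100,000 populations".

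On who is in the data, Randomization and recruitment says "Participants will recruit to the study when confirmed they have any form of TB and are registered to the DOT programs", and the sample size section says that "all cases that are confirmed as TB patients in the selected districts will be considered as the final sample size".

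Data analysis has two relevant steps. First: "Comparisons of detection rate, diagnosis delay, and costs of TB care between and within the intervention and control groups will be done", using independent-samples and paired t-tests. Second: "Logistic regression analysis will be used to determine the factors associated with case detection rate and diagnosis delay", with screening of variables by p-value, crude and adjusted odds ratios and a Hosmer–Lemeshow test. It also plans subgroup analysis of detection by patient or facility characteristics, and a covariate-adjusted analysis of detection. It ties the mixed model to the cost of care only, whereas the Abstract names mixed models for the outcome of interest in general.

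**The concern.** Logistic regression needs records with and without the event. Here the only individual records belong to people already diagnosed and registered, and those whom the health system missed are not observed. The case detection rate belongs to an area and a period, not to a patient.

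The formula raises a separate problem. A percentage of estimated cases must have estimated cases in its denominator, and the printed expression does not. Two statements of the primary outcome therefore disagree, and an analyst or a later reader cannot tell from the formula what was meant.

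At stake are a reproducible definition of the primary outcome and the promised adjusted analysis of it. Logistic regression is the only regression that Data analysis names for detection.

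**Working it through.** The protocol states no numerical detection rate, effect size or power for the primary outcome, so there is no figure of its own to reproduce.

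**Inputs**
- Incidence of 132 per 100,000 (Measurements).
- Zone population of about 2.6 million (Study settings).
- 13 districts plus 2 town administrations, three units randomised per arm (Randomization and recruitment).
- 39% of cases not reported or not diagnosed in the Amhara region (Background), so detection of about 61%.
- Assumption for illustration: 15 equal-sized units, so 2,600,000 / 15 = 173,333 people each.

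**Formula**
- Estimated cases: 132 / 100,000 × 173,333 = 228.8.
- Notified cases at 61%: 0.61 × 228.8 = 139.6.
- Verbal definition: 139.6 / 228.8 × 100 = 61.0%.
- Printed percentage formula, left to right: 139.6 / 100,100 × 173,333 × 100 ≈ 24,168 (unrounded count).
- If its total cases are read as the incidence figure instead: 132 / 100,100 × 173,333 × 100 ≈ 22,857. This is 100 times the estimated cases, and still not a percentage.
- Over populations of 100,000 to 2.6 million and true rates of 50% to 80%, the left-to-right reading runs from about 6,600 to 7.1 million.
- Effect of 100,100 alone: estimated cases become 132 / 100,100 × 173,333 = 228.57, and the rate moves from 61.00% to 61.06%.

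The fault is therefore the missing division. Multiplying incidence by population is right for the denominator, and the 100,100 slip is trivial in size.

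**Logistic model**
- With detection = 1 for every patient, the log-likelihood is the sum of log(p) over patients. It rises as the intercept goes to infinity, whatever the slopes, so no finite odds ratio is identified.
- A trial fit to 416 records with a constant outcome failed with perfect prediction and a singular matrix.
- Patient-characteristic subgroups fail for a related reason: the estimate is a rate per total population, and the protocol gives no expected cases by patient characteristic. Facility characteristics are different, because an area-level rate can be formed where a catchment population exists.

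**Arm comparison by t-test**
- On district rates: 3 + 3 − 2 = 4 degrees of freedom, critical t = 2.78.
- For assumed between-district standard deviations of 5, 10 and 15 percentage points, the difference detectable with 80% power is about 15, 31 and 46 points.

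**Incidence year**
- No 2023 figure is given. To show sensitivity only, take the 140 per 100,000 that Background gives for 2020: 61.0 × 132 / 140 = 57.5%, with the same number of notified cases.
- Within one year, a common incidence scales every district's rate equally. The between-arm ratio and the t statistic are then unchanged. A before-after comparison within an arm is not protected.

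**The case against.** A reader might infer that the primary outcome can be neither computed nor analysed. The documents do not support that. The definition is stated correctly in words twice, and with an incidence and a catchment population the rate follows. Data analysis names t-tests for the arm comparison separately, and these can be run on district rates. The logistic sentence concerns associated factors, an exploratory aim, so losing it leaves the arm comparison in place. Nor is a result in the thousands of percent a realistic outcome, since anyone obtaining it would see the error at once.

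A reader might also take the 2022 and 2023 estimates as a contradiction. They may simply be the denominators for the baseline and end-line periods, since the definition refers to the cases estimated for the year. That is an ambiguity to settle, not a shown error.

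Finally, a grouped model of notified out of estimated cases is possible in principle. The protocol does not describe one, however. Its denominator would be an external estimate, not a count of observed people, and notified cases could exceed it.

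All of this stands and limits the point. It does not rescue the printed formula, the patient-level logistic model or the patient-characteristic subgroups.

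**Conclusion.** Two stated elements are wrong as written and should be corrected before analysis. The percentage formula for the primary outcome contradicts the verbal definition (about 24,168 against 61% in the illustrative district). The logistic regression of detection, with the patient-characteristic part of the subgroup analysis, cannot be estimated. The first follows from setting the formula beside the definition; the second follows from the recruitment rule. Neither depends on the assumed district size or detection level, which only give a scale.

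The primary result remains obtainable from the verbal definition and the t-test. The weakness of that test depends on taking the randomised district as the unit and on the assumed standard deviations. No workable covariate-adjusted model for detection is stated: Data analysis offers only the logistic one, and the Abstract's broader mention of mixed models does not match it.

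**What to change.** 1. In both sections, replace the percentage formula with: case detection rate = notified cases / (incidence per 100,000 / 100,000 × catchment population) × 100. Correct 100,100 in the formula for estimated cases as well.
2. State which estimator year applies to which period, and use the same value in both arms. Also report the within-arm before-after comparison with the incidence held constant, so that a revised estimate cannot pass for a change in detection.
3. Drop logistic regression and patient-level subgroups for detection. Keep logistic regression for diagnosis delay, accounting for district.
4. For any adjusted analysis of detection, model district-level notified counts with log(expected cases) as offset, or use district log rates. Adjust for baseline and test at district level.

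The cost is protocol or analysis-plan wording; the register counts and population figures are needed for the rate anyway. The downside is precision: with six districts and terms for intercept, arm and baseline, 6 − 3 = 3 residual degrees of freedom remain, one fewer than for the unadjusted t-test.

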**Methods:**

A cluster randomized controlled trial will be conducted in northwest Ethiopia to determine the effectiveness of integrating traditional care with modern TB care. The intervention will be conducted in randomly selected districts in the South Gondar Zone. The control group will be an equal number of districts with usual care. The intervention comprised three key components, which include referral linkage from traditional to modern health care; training of health professionals and traditional care providers in three different rounds to increase their knowledge, attitude, and skills toward the referral systems; and TB screening at traditional health care sites. The primary outcomes of interest will be an increase in case detection rate, and the secondary outcomes of interest will be decreased diagnosis delays and catastrophic costs for TB patients. Data will be collected in both the intervention and control groups on the main outcome of interest and a wide range of independent variables. Generalized linear mixed models will be used to compare the outcome of interest between the trial arms, with adjustment for baseline differences.

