### Study design and participants

A parallel group cluster randomized controlled trial with two arms (i.e., intervention and control arms) will be conducted in six districts of the South Gondar Zone. The outcome of interest will be case detection rate, diagnosis delay, and catastrophic costs. The control arm will include the routine standard TB cares. In the intervention arm, TB-suspected individuals (i.e., people with coughs for more than 2 weeks, fever, chills, night sweats, anorexia, weight loss, chest pain, hemoptysis, lymphadenopathy, fatigue, or growth failure in children) will be identified by the traditional healer in traditional care centers (traditional healer clinics, holy water, mosques) and referred to modern health care centers (health facilities) where there is TB diagnostic service.

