#### Sample size calculation for cost of TB care among tuberculosis patients

To estimate the effect of integrating traditional care with modern care on the cost of TB care will be considered. The sample size will be calculated by using the two-sample comparison of proportions formula using STATA version 16. A chi-squared of the two independent samples will be used to calculate the sample size using household catastrophic cost incurred that catastrophic household expenditure of P1 = 40% [38] and assuming that the effect of the intervention on the cost of TB care decreased by 13% in the intervention group as compared to the control, P2 = 27% and using, 95% CI, power of 80%, and a type I error of 0.05, considering 10% non-response rate, the final sample size was 453. Since the study is a multicenter individually randomized trial, design effect will be used. According to the multicenter design effect formula, design effect formula is $$\mathrm{design\ effect}=\frac{\upsigma {e}^{2}}{\sigma {e}^{2}+\sigma {B}^{2}}$$ = 1 − *ρ*. The majority of formulas applied on multicenter design with better accuracy relative difference (ICC lesser than 0.052) for designs including more than 10 centers. Assuming that randomization will be balanced and stratified based on centers that have equal group sizes [37]. Assuming the variation between the centers is 0.05, design effect = 1 – *ρ* = 0.95. Therefore, the final sample size will be calculated as sample size * design effect 453 * 0.95 = 428 (214 in the intervention arm and 214 in the control arm).

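### The cost outcome is named two ways and sized as a proportion with catastrophic cost, but the analysis section specifies no test of that proportion, so the stated 80% power does not apply to the cost analysis as written.

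*Protocol article*

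**What the plan says.** **Naming.** The Methods part of the Abstract says "the secondary outcomes of interest will be decreased diagnosis delays and catastrophic costs for TB patients". Study design and participants agrees: "The outcome of interest will be case detection rate, diagnosis delay, and catastrophic costs". The second specific objective (end of Background) and Phase 4 (the end-line evaluation) speak of the cost of TB care or the cost of TB. Outcomes of interest says "The secondary outcomes of interests are diagnosis delay and costs of TB care" and goes on to describe direct and indirect amounts, with no threshold.

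**Definition.** Measurements makes catastrophic cost a yes/no variable: total cost "exceeding a given threshold of the household’s annual income, here defined as exceeding 20%, as recommended by WHO". Appendix 2 repeats the 20% threshold.

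**Sizing.** In the sample size section for cost of TB care, "The sample size will be calculated by using the two-sample comparison of proportions formula using STATA version 16". The inputs are 40% of households with catastrophic cost in the control arm, 27% in the intervention arm, 80% power, type I error 0.05 and 10% non-response.

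**Analysis.** Data analysis compares costs between arms by independent t-test and within arms by paired t-test. It then adds: "Generalized linear mixed models (GLMM) will be used to assess the impact of the intervention on the change of cost of TB care". No distribution or link is given. Logistic regression is assigned to case detection and diagnosis delay, and the chi-square test to baseline characteristics. Catastrophic cost does not appear in that section.

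**The concern.** The Data analysis section assigns methods outcome by outcome, yet the binary cost outcome that fixes the sample size receives none by name. Two things follow.

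First, the amount spent and the share of households above 20% of income are different quantities. A cost in dollars takes no account of household income. Mean cost can fall because a few very large bills shrink while few households cross the threshold, or stay flat while many cross it. A conclusion about catastrophic cost, which the Abstract promises, would then rest on a test of something else.

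Second, if the text can be read as testing either quantity, the choice can be made after the results are seen, and the stated power applies to only one of the two readings.

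**Working it through.** **1. Reproduce the stated sample size.** Inputs (sample size section for cost): p1 = 0.40, p2 = 0.27, two-sided alpha 0.05 (sidedness is not stated, but this fits), power 0.80. The mean proportion is 0.335.

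n per arm = [1.96 × √(2 × 0.335 × 0.665) + 0.842 × √(0.40 × 0.60 + 0.27 × 0.73)]² / 0.13² = (1.308 + 0.556)² / 0.0169 = 205.7, so 206 per arm and 412 in total.

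412 × 1.10 = 453.2, against the stated 453. The figure is therefore a two-proportion calculation, and its 80% is the power to detect 40% against 27%. The section then multiplies by 0.95 to reach 428 (453 × 0.95 is 430.35, a small slip). With 214 analysed per arm, the same formula gives 81.5% power. With 193 per arm after 10% non-response it gives 77.4%. Both ignore clustering.

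**2. Match each named method to the sized outcome.**

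| Method in Data analysis | Applied to | Tests the catastrophic-cost proportion? |
|---|---|---|
| Chi-square | Baseline characteristics | No |
| Independent and paired t-tests | Detection rate, delay, costs | No; these compare means |
| Logistic regression | Detection, delay | No; cost is not listed |
| GLMM | Change of cost of TB care | Not stated; no response scale or link |

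The only fully specified cost test is the t-test on costs.

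**3. Can the 80% be carried over to the amount?** Not from the document, which gives no mean, SD or difference in cost. As an illustration only, assume lognormal cost, the same income for every household, 206 per arm, no clustering, and a shift that turns 40% above the threshold into 27%. The shift in log cost is then (0.613 − 0.253) × SD = 0.36 × SD. Simulation (20,000 trials per row) gives:

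| Assumed log-SD | Power, t-test on raw cost | Power, proportion test | Trials where the two disagree on significance |
|---|---|---|---|
| 0.8 | 87% | about 80% | 16% |
| 1.0 | 81% | about 80% | 19% |
| 1.25 | 71% | about 80% | 26% |
| 1.5 | 60% | about 80% | 34% |

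The power of the t-test may lie above or below 80%, depending on an SD that the plan does not supply.

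**4. What would a test of the proportion deliver once district randomisation is respected?** Randomization and recruitment assigns three districts or towns to each arm. Take 206 per arm, so about 68.7 patients per district, and assume equal sizes. The design effect is 1 + (68.7 − 1) × ICC. The SE of the difference is √[(0.24 + 0.1971)/206 × design effect], and the test is a t-test on 4 degrees of freedom.

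| Assumed ICC | Design effect | SE | 0.13 / SE | Power |
|---|---|---|---|---|
| 0.01 | 1.68 | 0.060 | 2.18 | 39% |
| 0.03 | 3.03 | 0.080 | 1.62 | 24% |
| 0.05 | 4.38 | 0.096 | 1.35 | 18% |

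The article gives no district-level ICC for cost. It uses 0.03 for detection rate and 0.05 for between-centre variation, which fall inside this range.

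**The case against.** A reader might infer that every planned analysis compares mean cost and that the catastrophic proportion is never tested. The article does not support that. A generalized linear mixed model can be logistic, and none of its details are fixed. The sample size section itself uses cost of TB care as the label for the binary measure, so the same phrase under Data analysis need not mean an amount. The Abstract lists catastrophic costs and then applies GLMMs to the outcome of interest. The link function may also sit in an analysis plan that is not shown. All of this stands.

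It is also fair that the objectives, Phase 4 and Outcomes of interest name cost itself, so Data analysis agrees with those parts. The fault is inconsistency between sections; it is not simply that the analysis departs from an agreed outcome.

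The simulated figures in step 3 carry little weight. The log-SDs are assumed and a common income is imposed. If income is instead allowed to vary independently of cost (assumed income log-SD 0.7 to 0.8, cost log-SD 0.8 to 1.0), the power of the raw-cost t-test rises above 90%. The article also plans normality and outlier checks, although it states no action to follow from them.

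What the objection does not remove: two names for the outcome, a sample size tied to one of them, and an analysis section that uses logistic regression by name for other outcomes but says nothing of how the sized proportion is compared between arms. A missing link function can be left to an analysis plan. A conflict over which variable is the outcome is visible in the article itself.

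**Conclusion.** The point holds in this form: the cost outcome is named in two ways, it is sized as a proportion, and the analysis section specifies no test of that proportion. The 80% is reproduced exactly as power for 40% against 27% without clustering, and nothing in the article transfers it to the t-test on costs or to a GLMM of unstated form.

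This rests on the text and on the reproduction of 453. It does not depend on the simulation, which shows only that the two tests can differ in power in either direction. The power of 39% to 18% for a district-level test depends on the assumed ICCs, equal district sizes and 206 analysed per arm. The main cause of that shortfall is the three-per-arm cluster design, which is a separate matter, but it means that naming the proportion as the outcome will not by itself restore 80%. The outcome is secondary and wording is enough to settle it, so this should be corrected but is not critical to the trial.

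**What to change.** - Name one cost outcome and use it in the Abstract, the specific objectives, Study design and participants, Phase 4, Outcomes of interest, the cost sample size section and Data analysis. As the trial is sized, it is the proportion of patients whose total cost exceeds 20% of annual household income.
- In Data analysis, compare that proportion between arms by a method that respects district randomisation: for example, district-level proportions, or a logistic mixed model with a small-sample correction for three districts per arm.
- Keep the cost amount as a supportive analysis.
- In the sample size section, say that the 80% ignores clustering and will not be reached by a district-level test.

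**Cost.** The change is to wording only, since cost and income are already collected. The price is a less favourable stated power for this outcome.
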